#### Objective 3. Evaluate the accuracy and coverage of the proposed wireless technology as compared to standard monitoring technology in the NICU

Accuracy will be assessed by comparing both the contents and the quality of the data obtained by the ANNE^®^ sensors and the standard monitoring technology.

In terms of the contents, the recorded data of the raw heart rate (HR), temperature, oxygen saturation (SpO_2_), and respiratory rate (RR) obtained by the ANNE^®^ sensors will be compared to the raw signals obtained by the standard monitoring system. A detailed list of the statistics that will be obtained from the data for comparison can be found in Table 3.

**Table 3 table-3:** List of desired test statistics derived from raw monitor signals.

Heart rate	Average heart rate per epoch (*via* histogram); number of bradycardias and tachycardia per hour; average and maximal duration of bradycardias (<100 beats/min) and tachycardia (>160) per recording (8-h epoch in phase I, 24-h epoch in phase II); number of bradycardias and tachycardia >10 s per hour or per epoch; average heart rate per epoch (*via* tachogram).
ECG (time domain metrics)	minimum, maximum, and median NN interval (*i.e*., the interval between successive R-waves); standard deviation of the NN intervals (SDNN); the standard deviation of the averages of NN intervals in all 5-min segments of the recording (SDANN); the mean of the standard deviations of all NN intervals for all 5-min segments of the recording (SDNNi); the percentage of adjacent NN intervals differing by >50 ms (pNN50); root mean square of successive differences of NN intervals (RMSSD); total number of all NN intervals divided by the height of the 32-bin histogram of all NN intervals (triangular index; HRVTi); and the baseline width of the minimum square difference triangular interpolation of the highest peak of the 32-bin histogram of all NN intervals (TINN).
ECG (frequency domain metrics)	TP: total power (<0.4 Hz), VLF: very low frequency (<0.04 Hz), LF: low frequency (0.04–0.15 Hz), HF: high frequency (>0.15 to <0.4 Hz), and LF/HF ratio using the Welch periodogram
Oxygen saturation	Average, median and interquartile range of SpO_2_ and percentiles (5^th^ and 95^th^); percentage time with values in 5% groupings between 70% and 100%; percentage times spent with SpO_2_ below 80% and above 95%; values in 5% groupings between 70% and 100%
Respiratory rate	Average value (*via* histogram), number of bradypnea (<40 breaths/min) and tachypnea (>60 breaths/min) per hour; average and maximal duration of bradypnea and tachypnea per recording (8-h epoch in phase I, 24-h epoch in phase II); number of bradypnea and tachypnea >10 s per hour or per epoch; standard deviation, correlation, …tachypnea (above 60), bradypnea (below 40)
Temperature	Average temperature; measurements of temperature variability (using standard deviation of the daily average temperature); percentage times spent in hypothermia (temperature <36.0 °C) and hyperthermia (temperature > 37.5 °C)

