### Eligibility criteria

Three different age groups will be included: Group 1 = term infants (37^+0^ to 40^+6^ weeks); Group 2 = preterm infants with postmenstrual ages 28^+0^ to 36^+6^ weeks, and Group 3 = extremely preterm infants with postmenstrual ages 23^+0^ to 27^+6^ weeks. Groups were designed by neonatologist to reflect a variety of common clinical situations encountered in the NICU. Each age group will consist of a variety of subgroups based on different clinical criteria for inclusion (Table 1). Infants with congenital anomalies and surgical conditions (gastroschisis, omphalocele, congenital diaphragmatic hernia), congenital heart disorders, will be excluded to reduce interference of research with care, and reduce interruptions in data collection. Additionally, infants congenital skin infections or known conditions with fragile skin (such as *epidermolysis bullosa*) will be excluded to prevent additional discomfort or complications associated with adhesives. See Fig. 1 for enrollment plan.

**Table 1 table-1:** Study population characteristics.

Groups	Clinical characteristics	Phase 1 (*n* = 24)	Phase 2 (*n* = 24)
Group 1—Term infants with postmenstrual ages at enrollment of 37–42 weeks’	***A:*** healthy* infants in room air at enrollment (*N* = 6)	3	3
	***B:*** infants with perinatal asphyxia undergoing therapeutic hypothermia at enrollment (*N* = 6)	3	3
Group 2—Preterm infants with postmenstrual ages at enrollment of 28^+0^ to 36^+6^ weeks	***C:*** healthy* infants in room air at enrollment (*N* = 6)	3	3
	***D:*** infants on continuous positive airway pressure at enrollment (*N* = 6)	3	3
Group 3—Preterm infants with postmenstrual ages at enrollment of 23^+0^ to 27^+6^ weeks	***E:*** infants on conventional mechanical ventilation at enrollment (*N* = 6)	3	3
	***F:*** infants on high frequency ventilation at enrollment (*N* = 6)	3	3
	***G***: infants on nasal intermittent positive end expiratory pressure at enrollment (*N* = 6)	3	3
	***H***: infants on continuous positive airway pressure at enrollment (*N* = 6)	3	3
**Total:**		24	24

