**Figure 3 fig-3:**
[figure not shown]
ANNE^®^ one wireless sensors. Two devices comprising ANNE^®^ One monitoring system and signals to be acquired by the chest and limb sensors. ANNE^®^ One chest obtains electrocardiography, accelerometry, and temperature. ANNE^®^ One limb: obtains photoplethysmography, temperature. Image provided and approved for publication by Sibel Inc. (Chicago, IL, USA).

Sensor 1—A chest unit (ANNE^®^ Chest) with embedded battery, ECG electrodes, clinical grade thermometer, and a three-axis accelerometer that captures the following signals: electrocardiography (ECG), temperature, and chest wall movements. The sensor will be placed in the middle of the infant’s chest.

Sensor 2 (phases 1 and 2)—A limb unit (ANNE^®^ Limb) with embedded battery, clinical grade thermometer, and two LEDs along with a photodiode that capture photoplethysmogram (PPG) at each wavelength of light, from which the SpO_2_ is calculated. The sensor will be placed on either ankle-to-base of the foot or the wrist-to-hand, with rotations done as per standard of care (every 4 h for preterm infants and every 12 h for term infants).

Sensor 3 (phase 2 only) An abdominal unit (ANNE^®^ Chest) with embedded battery, sensors, and a three-axis accelerometer that captures the following signals: electrocardiography (ECG), temperature, and abdominal wall movements. Only signals of abdominal wall movements will be sampled. The sensor will be placed above the umbilical line.

During the monitoring periods a Biosensors Data Aggregation and Synchronization (BioDASh) system developed by iKinesia Inc (Montreal, Quebec, Canada) for this study will simultaneously record the vital signals from both systems: wired and wireless. The only vital sign recording that will not be recorded continuously by BioDash is the standard temperature which is recorded using a clinical grade handheld thermometer or by a temperature sensor adhesive connected to the incubator. The reasons for this are: (a) temperature is not continuously recorded in all patients in the NICU and (b) BioDash is not able to connect and record signals from to the incubator.

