#### Study phases

**Phase 1**: Clinical and physiological data will be continuously acquired for 8 h during daytime, for 4 consecutive days. The wireless sensors will be visually assessed and disinfected using 70% isopropyl wipes prior to placement and following device removal each day of the study. Sensors will be disinfected using the same solution at the end of the study.

The ECG and SpO_2_ leads will be connected to a Philips Intellivue monitor (Intellivue MX450; Philips Healthcare, Best, Netherlands) to capture ECG and HR, PPG, SpO_2_, and respiratory waveform and rate data to be displayed and exported in real-time using a direct cable connected to a personal laptop computer *via* MediCollector software (Boston, MA, USA). At the beginning of each day, ANNE^®^ sensors are selected for pairing by the researcher with the BioDash recording system based on serial number displayed both on tablet and devices. Data from the paired ANNE^®^ sensors will be transferred *via* Bluetooth to a study tablet which will simultaneously send this data to the study laptop. The following waveforms and vital signs from both systems (*via* Philips Intellievue MX450) and ANNE^®^ sensors will be recorded: ECG and heart rate, PPG, SpO_2_, respiratory waveform and respiratory rate signals. In addition, body temperature will be recorded from ANNE^®^ sensors only. The BioDASh application running on the study laptop will stream, display, and log data in real-time. In addition, photographs of the skin at the site of placement of the sensors will be taken at baseline, time of device removal.

**Phase 2**: Clinical and physiological data will be acquired for 96 consecutive hours. The sensors will be replaced every 24 h or whenever low battery is detected. The wireless sensors will be visually assessed and disinfected using 70% isopropyl wipes prior to initial device placement, at each replacement, and following device removal at the end of the study. The same signals as in Phase I will be recorded by the BioDash Application.

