#### Objective 3: Evaluate the accuracy of proposed wireless technology as compared to standard monitoring technology in the NICU

To evaluate the accuracy of the ANNE^®^ we will compare the data obtained by the wireless system to the standard of care. The number of data points acquired for comparison during each hour of participation in either phase 1 or 2 is shown in Table 5. Total number of data points acquired per hour and throughout the entire study are provided in Tables S2 and S3. To comprehensively describe how ANNE^®^ compares to the Phillips monitor, several signal processing and statistical methods have been selected following an extensive literature review. These techniques have been separated into four classes, according to their overall objective: (1) methods that describe signal quality (2) methods that describe the continuity of the data, (3) methods that compare the raw signals from ANNE^®^ and Phillips directly, and (4) methods that compare summary statistics derived from these signals. A list of the statistical methods that will be utilized are outlined in Table 6.

**Table 5 table-5:** Expected number of data points obtained per participant per hour.

	Philips intellivue MX450	Wireless ANNE^™^ monitoring system
ECG	1.8 × 10^6^	9.207161125 × 10^5^
PPG	4.5 × 10^5^	2.303262956 × 10^5^
Resp signal	2.25 × 10^5^	1.152 × 10^5^
HR	3.515625 × 10^3^	3.6 × 10^3^
SpO_2_	3.515625 × 10^3^	3.6 × 10^3^
RR	3.515625 × 10^3^	3.6 × 10^3^
Temperature (axial & chest respectively)*	1	9 × 10^2^
Skin temp. limb	N/A	9 × 10^2^
3-axis Accel.	N/A	1.5 × 10^6^
Total	2.485547875 × 10^6^	2.778842408 × 10^6^

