**Note:**

* Temperature is recorded manually by nurse every hour.

**Table 6 table-6:** Analytical methods to be implemented.

Measure	Applicable methods
Signal quality	Time-warped polynomial filtering (TWPF) Signal averaging Probability distribution function (PDF) Power spectrum
Continuity of the signal	FIR antialiasing lowpass filtering Movement artifact removal Data segmentation
Direct comparison of the raw signals	Cross-correlation function Probability distribution function (PDF) Power spectrum Impulse response function (IRF) Box-jenkins system identification Bland-altman method Lin’s concordance correlation coefficient (CCC) Intraclass correlation coefficient (ICC) Paired *t*-test Equivalence testing
Comparison of derived statistics/signals	Lin’s concordance correlation coefficient (CCC) Intraclass correlation coefficient (ICC) Paired *t*-test Equivalence testing ANOVA *F*-test

Table 5 Expected number of data points obtained per participant per hour.

Quality of the signals—by quantifying the noise level of each device. This will be accomplished *via* signal averaging and time-warped polynomial filtering (TWPF). Both methods attempt to clean a noisy signal such as an ECG and produce a deterministic product. By removing this deterministic component from the raw signal, a noise signal may be obtained for each device. Statistical parameters including variability metrics and the signal-to-noise ratio (SNR) will be used to describe the overall quality of each device for measuring vital signals. These parameters will be accompanied by appropriate probability density functions (PDF) and power spectra.

Continuity of the signals—pre-processing will be used to divide the data into segments of connection loss, corruption due to significant movement artifact, and usable portions of signal recordings. From here, a set of statistics can be used to describe the technical reliability of ANNE^®^, including the number and duration of interruptions, the average period between consecutive interruptions, as well as the portion of data deemed unreliable due to increased movement. Small segments of interruption (<2 s) will be interpolated to yield longer segments of continuous monitoring. Performing this analysis on the data acquired from both phases will further allow us to study how increasing recording length potentially exacerbates these statistics.

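### Temperature is planned as a raw-signal comparison with time-in-range statistics, but its reference is about one manual reading per hour

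*Protocol article*

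**What the plan says.** All places are in the Protocol article.

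- **Outcomes, Objective 3.** Temperature is one of four vital signs whose ANNE data "will be compared to the raw signals obtained by the standard monitoring system". The reader is sent to Table 3, whose title describes statistics derived from raw monitor signals.
- **Table 3, Temperature row.** It asks for the average, the SD of the daily average, and "percentage times spent in hypothermia (temperature <36.0 °C") together with the share of time above 37.5 °C.
- **Study equipment.** "The only vital sign recording that will not be recorded continuously by BioDash is the standard temperature". That temperature is "recorded using a clinical grade handheld thermometer or by a temperature sensor adhesive connected to the incubator", and BioDASh cannot connect to the incubator.
- **Study phases, Phase 1.** "body temperature will be recorded from ANNE^®^ sensors only".
- **Table 5.** The row "Temperature (axial & chest respectively") shows 1 value per hour in the Philips column and 900 in the ANNE column. Its note reads: "Temperature is recorded manually by nurse every hour". Limb skin temperature has no reference (N/A).
- **Device data collection forms, and Table 4.** Both describe an hourly axillary (in Table 4, axial) reading by the nurse.
- **Statistical methods, Objective 3.** ANNE data are resampled to the number of Philips points. Bland-Altman, paired t-tests and correlation coefficients are then applied. Table 6 lists CCC and ICC for both raw and derived comparisons.
- **Table 1, subgroup B.** Six of the 48 infants are "infants with perinatal asphyxia undergoing therapeutic hypothermia at enrollment".

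**The concern.** Accuracy is part of the primary outcome in the Abstract, and temperature is one of the four vital signs compared. The Objective 3 text treats it like the other three, yet by the article's own account no reference signal exists for it, only spot readings.

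Two things follow if the text is carried out as written. First, percentage time in hypothermia or hyperthermia would be computed from a dense series for one device and a handful of readings for the other. A gap between them would partly measure sampling frequency rather than sensor error. Second, the reference may come from either of two instruments under one description and from an hourly axillary reading under another, while the ANNE value comes from the chest. Differences of instrument and site would be mixed with sensor error unless the reference type is known for each pair.

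There is also a conditional risk. CCC and ICC grow with the spread between infants, and a deliberately cooled subgroup widens that spread.

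**Working it through.** **1. The plan's own figures.** The Table 5 totals reproduce only with one reference temperature per hour.

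- Philips: 1,800,000 + 450,000 + 225,000 + 3 × 3,515.625 + 1 = 2,485,547.875, as printed.
- ANNE: 920,716.1125 + 230,326.2956 + 115,200 + 3 × 3,600 + 900 + 900 + 1,500,000 = 2,778,842.408, as printed.

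The ratio of 1 to 900 is therefore the plan's intention, not a misprint.

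**2. Resolution of reference percentage time.** With n readings the step is 100/n.

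- 8-h recording: 100/8 = 12.5 points, against 8 × 900 = 7,200 ANNE chest values.
- 24-h epoch: 100/24 = 4.2 points.
- Full participation: 100/32 = 3.1 points (phase 1) and 100/96 = 1.0 point (phase 2).

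Table 3 states the 8-h and 24-h units in the heart rate and respiratory rate rows. Using them for temperature is an assumption.

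**3. Missed excursions.** For regular hourly readings and a single excursion of L minutes (L < 60) at a random time, the probability of a miss is 1 − L/60.

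| L (min) | Probability missed |
|---|---|
| 10 | 0.83 |
| 20 | 0.67 |
| 30 | 0.50 |
| 45 | 0.25 |

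Example: one 30-min excursion in 8 h is 30/480 = 6.25% of the time. A perfect sensor reports 6.25%. The reference reports 0% or 12.5%, each with probability 0.50. The devices differ by 6.25 points either way with no sensor error. If reading times are unrelated to the infant's temperature, this averages out over many recordings (0.50 × 12.5 = 6.25). What suffers is agreement per recording, not necessarily the mean difference.

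**4. What the hourly readings can support.** With complete follow-up, phase 1 gives 24 × 32 = 768 pairs and phase 2 gives 24 × 96 = 2,304. Together that is 3,072 pairs, repeated within infant.

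**5. CCC and ICC if all infants were pooled.** The article gives no temperatures, SDs or bias, so these are assumptions. Let p = 6/48 = 0.125, d = cooling offset, SD = between-infant SD of the others, b = bias, s = error SD.

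- V = SD² + p(1 − p)d²
- CCC = 2V/(2V + s² + b²)
- Consistency ICC = V/(V + s²/2), with error on the sensor only

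One case, with SD = b = s = 0.3 °C and d = 3 °C:

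- Without cooled infants: V = 0.09; CCC = 0.18/0.36 = 0.50; ICC = 0.09/0.135 = 0.67.
- Pooled: V = 0.09 + 0.109375 × 9 = 1.074; CCC = 2.149/2.329 = 0.92; ICC = 1.074/1.119 = 0.96.
- Bland-Altman half-width: 1.96 × 0.3 = 0.59 °C in both. A simulation of 48 infants gave CCC 0.92 and 0.49, and half-widths 0.585 and 0.584.

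Range, with SD 0.2–0.4, b 0–0.5, s 0.3–0.5 and d 2–3.5 °C: CCC is 0.14–0.78 without cooled infants and 0.66–0.97 pooled. If infants are cooled for only half the recording, pooled CCC is 0.52–0.95.

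**The case against.** The strongest reply is that the plan discloses the sparse reference. Table 5 is introduced as the data points acquired for comparison and pairs the axillary reading with the chest sensor at 1 against 900. The hourly reading is collected, ANNE is resampled to the reference's number of points, and Bland-Altman is listed. That stands. A reader might infer that temperature accuracy cannot be assessed at all, and the documents do not support this. What fails is the raw-signal description and the time-in-range comparison. Resampling does not settle the latter, because the text neither applies it expressly to temperature nor restricts percentage time to matched readings.

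Other stronger readings are also unsupported:

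- **That the plan pools cooled infants.** The Statistical methods do not say whether it does, and subgroup handling may sit in an analysis plan not shown. Table 6 is a general list of methods, not assigned to each vital sign.
- **That the 36.0 and 37.5 °C limits are applied to the limb sensor.** No section says so, and Table 5 gives limb temperature no reference.
- **That subgroup B's low temperatures are in themselves a comparison defect.** Both devices would register them.
- **That the SD of daily averages cannot be computed.** It can, from 8 or 24 readings a day.
- **That a usable recording may hold only about 2 reference values.** This assumes that the 2-h rule for paired ANNE and Philips data governs temperature, which is not stated.

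The size of any ICC effect also depends on the error model. With SD 0.3, error SD 0.5 and d = 3.3 °C, placing the full error variance on both methods gives 0.26 without and 0.84 with the cooled infants. Placing it on the sensor alone gives 0.42 and 0.91. The direction is the same.

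**Conclusion.** The point holds in limited form and should be corrected. The description of temperature as a raw-signal comparison contradicts the article's account of how the reference is obtained. That part needs no assumption. Percentage time is not comparable between devices as written: the reference resolution is 12.5 points per 8 h or 4.2 per 24 h, if the recording units used elsewhere in Table 3 apply. The miss probabilities assume regular readings and a single excursion.

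The reference instrument is inconsistent. Study equipment allows a handheld thermometer or an incubator-connected adhesive probe, while the data collection forms and Tables 4 and 5 describe an hourly axillary reading. The Background mentions an axillary probe, so one site with two instruments may be meant, but the text does not say so. These places must be reconciled.

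The effect on CCC and ICC is a conditional risk: its direction is certain if infants are pooled while cooled, but its size rests wholly on assumed temperatures, SDs and cooling time. Bland-Altman limits do not change in the same calculation.

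**What to change.** - In the Objective 3 text under Outcomes, in Table 3 and in the raw-signal paragraph of Statistical methods, state that temperature is compared only as time-matched pairs: the ANNE chest value averaged over a short fixed window around each manual reading.
- Analyse the pairs by Bland-Altman for repeated measures within infant.
- Reconcile the descriptions of the reference. Record the reference type for each reading and use it as a factor.
- Drop percentage time below 36.0 °C and above 37.5 °C as a between-device comparison, or compute it for both devices from the matched readings only.
- Compute the average and the day-to-day SD from matched readings.
- Report bias and limits separately for subgroup B and for the other infants, and do not rely on a pooled ICC or CCC for temperature.

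The cost is wording and analysis code. The hourly reading is already on the data collection form. Whether the form also holds the instrument and exact time cannot be seen in the article; if not, those fields must be added. The downside is fewer temperature metrics and possibly a lower reported ICC or CCC.

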Compare the raw signals from ANNE^®^ and Phillips directly—a preliminary step requires that the signals from ANNE^®^ be resampled to produce segments with an equal number of data points as the Philips monitor (this will be completed as part of the pre-processing in the second class of analysis). Any recording period with under 2 h of usable paired data from the ANNE^®^ and the Phillips will be excluded from comparative analysis. Once equal data samples have been obtained from all usable recordings, the cross-correlation will be used to quantify the latency between matching signals. Performing this operation on segmented epochs throughout a recording will also allow us to determine whether the delay varies with monitoring time or remains constant. The length of epoch segments will be determined based on preliminary analysis. In the time domain, the (PDF) will be used to compare the amplitude structures of signals, while system identification *via* linear models will be used to study the relationship between ANNE^®^ and the Philips monitor. In the frequency domain, the power spectrum will be derived to compare the frequency contents of each signal and extract statistics for the third class of techniques. Lastly, statistical methods, such as the Bland-Altman method, paired *t*-tests, and correlation coefficients, will be implemented to evaluate the agreement between paired measurements or samples.

Compare summary statistics—from the raw signals, summary statistics will be derived and compared to further validate the reliability of ANNE^®^. A detailed list of statistics, both in the time domain and frequency domain, for the various vital signals are outlined in Table 3 alongside traditional measures such as the average heart rate over a specified period, the average respiratory rate over a specified period, and the number of heart beats or breaths detected and/or missed by each device. Graphical representations of desired statistics used for analysis are shown in Fig. 5. The same statistical procedures previously mentioned will be applied once more, this time comparing paired statistics as opposed to matching sample points.

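### Bradycardia, tachycardia, bradypnea and tachypnea are compared only as counts and durations per device, so no planned output shows whether the two devices flagged the same episode

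*Protocol article*

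**What the plan says.** Table 3 (Outcomes, Objective 3) lists the statistics to be derived from each device. For heart rate these include "number of bradycardias and tachycardia per hour; average and maximal duration of bradycardias" and "number of bradycardias and tachycardia >10 s per hour or per epoch". For breathing they include "number of bradypnea (<40 breaths/min) and tachypnea (>60 breaths/min) per hour" and "number of bradypnea and tachypnea >10 s per hour or per epoch". Durations are summarised per recording, which the table takes as 8 h in phase 1 and 24 h in phase 2.

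Statistical methods, Objective 3, then says how the derived statistics are compared: the procedures used for the raw signals are applied again, "this time comparing paired statistics as opposed to matching sample points". For derived statistics, Table 6 lists Lin's CCC followed by "Intraclass correlation coefficient (ICC) Paired *t*-test Equivalence testing ANOVA *F*-test".

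Two other planned analyses bear on the point. The raw signals are compared directly with Bland-Altman, paired t-tests and correlation coefficients, which "will be implemented to evaluate the agreement between paired measurements or samples". The summary statistics also include "the number of heart beats or breaths detected and/or missed by each device".

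**The concern.** A count per hour records how many episodes a device flagged, not which ones. If the wireless system misses some true episodes and flags about as many that did not occur, the two counts have the same mean. A paired t-test or an equivalence test on the mean then has nothing to detect. CCC and ICC do penalise the scatter, but they weigh it against the spread of event rates between infants. Table 1 makes a wide spread plausible, since it runs from healthy term infants in room air to extremely preterm infants on ventilation. Averaging over a long recording shrinks the scatter further and leaves the spread untouched.

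At stake is how the accuracy result is read. The article's discussion presents re-evaluation of this technology as an essential step towards its use as standard of care. Close agreement in event counts could be taken as evidence of reliable episode detection, and no planned output would confirm or refute that.

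**Working it through.** **Figures in the plan.** The article states no event rate, miss rate, agreement threshold or equivalence margin, so there is no figure to reproduce. The 48 infants and the 8-h and 24-h recordings come from the article. All rates below are assumptions.

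**Model.** Infant i has true rate λ_i per hour. The reference hourly count is N ~ Poisson(λ_i). The wireless count is Binomial(N, 0.6) + Poisson(0.4 λ_i): 40% missed, and as many false episodes on average. Sensitivity and positive predictive value are both 60% by construction.

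**Mean difference.** 0.6 λ_i + 0.4 λ_i − λ_i = 0. In simulations of 24 infants over 4 days, across mean rates of 0.5 to 10 per hour and between-infant coefficients of variation of 0 to 1.5, the paired t-test on per-recording rates rejected in 0 to 9% of runs.

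**CCC.** With mean rate m, between-infant variance v and h hours averaged:

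CCC = (v + 0.6 m/h) / (v + m/h)

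For a log-normal rate with median 1.5/h and log-SD 1.0:
- m = 1.5 × e^0.5 = 2.47
- v = m² × (e − 1) = 10.51
- h = 1: (10.51 + 1.48)/(10.51 + 2.47) = 0.92
- h = 8: (10.51 + 0.185)/(10.51 + 0.309) = 0.99
- h = 24: (10.51 + 0.062)/(10.51 + 0.103) = 0.996

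These are large-sample values. In samples of 48 infants the observed variance of a skewed rate usually falls below v, so simulated CCCs (2,000 studies) are slightly lower:

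| Assumed spread | Single hours | 8-h rates | 24-h rates |
|---|---|---|---|
| log-SD 1.0 | 0.90 | 0.98 | 0.99 |
| log-SD 0.5 | 0.72 | 0.91 | 0.96 |

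With no spread between infants (v = 0) the formula gives 0.60 whatever the recording length. Over the wider grid of m and coefficient of variation above, single-hour CCC runs from 0.60 to 0.98.

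**False episodes unrelated to the infant's own rate.** If every infant has the same false-episode rate, 0.4 m:

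CCC = 1.2 (v + m/h) / (1.36 v + 2 m/h)

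This is at most 1.2/1.36 = 0.88. With log-SD 1.0 it gives 0.81 for single hours (15.58/19.24) and 0.87 for 8-h rates (12.98/14.91).

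**What the other planned outputs would show.**
- Bland-Altman on hourly counts: the SD of the difference is √(0.8 × 2.47) = 1.41, so the limits are about ±2.8 episodes around a mean of 2.5.
- Raw heart rate: at 1.5 episodes/h of 15 s (assumed), episodes fill 1.5 × 15/3600 = 0.625% of the time. The 40% missed and the equal false share together affect 0.8 × 0.625% = 0.5% of samples. For errors of 40 to 60 beats/min (assumed), the limits are 1.96 × √(SD² + 0.005 × error²). With a baseline SD of 2 they widen from ±3.9 to ±6.8–9.2. With an SD of 5 they widen from ±9.8 to ±11.3–12.9.

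None of these results converts back into a share of episodes missed or invented.

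**The case against.** The strongest reply is that the plan would not be blind to such a device. Raw heart rate and respiratory rate are compared sample by sample, and the limits above widen visibly when the baseline noise is low. The text carries the raw-signal procedures, which include Bland-Altman, over to the derived statistics, although Table 6 lists Bland-Altman only for raw signals. Limits of ±2.8 around a mean of 2.5 would look poor, and they do not rely on spread between infants. The count of beats or breaths detected or missed also bears on the fault, since a device that hides a bradycardia must register extra beats. All of this stands. It means part of the fault would appear as scatter. It does not supply the missing quantity, because beats and breaths are not episodes and wide limits do not separate missed episodes from false ones.

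A reader might infer that event counts will agree almost perfectly whatever the device does. The documents do not support that: on single-hour counts CCC can be as low as 0.60, and values near 1 need long averaging, very different infants and false episodes that follow each infant's rate. A reader might also infer that raw limits of agreement would hardly move, or that the plan would declare such a device accurate. The first holds only approximately, and only with a noisy baseline. The second is not in the article, which sets no CCC threshold and presents the study as exploratory.

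It can also be said that matching details belong in an analysis plan not shown here. A window width might. But Table 3 and the methods text do state how events are to be compared, and that stated choice is the point at issue.

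**Conclusion.** The point holds in a conditional form. Event agreement is planned on counts and durations only, and nothing in the article matches episodes between devices. Under the stated assumptions, a device with 60% sensitivity and 60% positive predictive value shows no mean difference and a CCC of about 0.90 on single hours, 0.98 on 8-h rates and 0.99 on 24-h rates. These fall to 0.72, 0.91 and 0.96 with half the log-SD, and CCC cannot be expected to exceed 0.88 if false episodes occur at the same rate in every infant. The 40% miss rate and the event rates are illustrative. The absence of any episode-level output does not depend on them.

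**What to change.** In Table 3, and in the part of Statistical methods, Objective 3, on comparing summary statistics, add a time-matched episode analysis:

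- Define episodes by the thresholds already in Table 3, with its class of events longer than 10 s.
- Correct for the latency that the plan already estimates by cross-correlation.
- Pair each Philips episode with a wireless episode inside a matching window fixed before the data are analysed.
- Report sensitivity, positive predictive value and false episodes per hour against the Philips reference, by event type, with intervals clustered by infant.
- Keep the counts and durations as description.

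The cost is some extra analysis code. Both streams are already synchronised in BioDASh and stored unfiltered, so no new data, infants or procedures are needed.
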